### Participants information

2.8

Information collected during the screening period will include demographic data (date of birth, gender, ethnicity); TD-related information, including the date of initial diagnosis, date of first medical consultation for TD-related symptoms, frequency and type of past symptoms, disease subtype (TTD, CTD, TS), and a history of prior pharmacological and non-pharmacological treatments for TD; as well as medical history unrelated to TD, a history of pharmacological and non-pharmacological treatments within the 3 months prior to screening, and allergy history.

### Preparation of study medications

2.9

PABG (Batch No.: Yue Z20070083) and the active control used in this study will be uniformly prepared and packaged by the Shenzhen Traditional Chinese Medicine Preparation Center. Both will be verified as compliant prior to use, with each sachet containing 10 g. The active control herbal preparation has been validated in previous studies (41). The ingredients and quantities for PABG are presented in Table 2. All herbal ingredients will be sourced from government-authorized TCM suppliers. Each herb will undergo testing for microbiological contamination, heavy metals, and pesticide residues to ensure compliance with Chinese regulatory requirements, with the entire quality assessment process overseen by senior TCM practitioners.

**Table 2 tab2:** Ingredients and quantities for 100 sachets (1,000 g) of PABG.

Herbal name (Latin & Vernacular)	Quantity (g)
Acorus tatarinowii (Shi-Chang-Pu)	250
Poria cocos (Fu-Ling)	165
Fructus Tritici levis (Fu-Xiao-Mai)	250
Astragali radix (Huang-Qi)	165
Hordei fructus Germinatus (Mai-Ya)	250
Citri reticulatae pericarpium (Chen-Pi)	85
Arisaema cum bile (Dan-Nan-Xing)	165
Corni fructus (Shan-Zhu-Yu)	165
Lapis chloriti (Qing-Meng-Shi)	250
Notopterygii rhizoma et radix (Qiang-Huo)	85
Massa Medicata Fermentata (Liu-Shen-Qu)	165
Polygalae radix (Yuan-Zhi)	165
Aurantii fructus (Zhi-Qiao)	165
Alpiniae oxyphyllae fructus (Yi-Zhi-Ren)	165
Crataegi fructus (Jing-Shan-Zha)	165
Glycyrrhizae radix et rhizoma (Gan-Cao)	165
Pinellia Ternata (Qing-Ban-Xia)	165
Haliotidis concha (Shi-Jue-Ming)	250
Sucrose	680
Dextrin	227
In total	4,142

The 18 Chinese herbal decoction pieces in the prescription will be decocted twice in water, each time for 2 h. The decoction liquids will be combined and filtered, and the filtrate will be concentrated to a clear paste with a relative density of 1.25–1.30 (measured at 80 °C). After cooling, 1,500 mL of ethanol will be added, stirred thoroughly, and allowed to stand for 24 h. The supernatant will be decanted to recover ethanol and then reconcentrated to a clear paste with a relative density of 1.25–1.30 (measured at 80 °C). Sucrose powder and dextrin will be added, mixed uniformly, granulated, and dried at 65–75 °C to produce 1,000 g. The raw material–to–product weight ratio in this process is approximately 4:1. The active control preparation contains 5% of the active ingredients of PABG, termed the minimal-dose active control, with caramel color and chocolate brown pigment added in an 8:3 ratio to ensure a consistent appearance, taste, weight, and smell with PABG. The formulation center will uniformly package all investigational medicinal products in compliance with relevant Chinese pharmaceutical regulatory requirements, labelling them as “Drug A” and “Drug B” to maintain the double-blind design.

The 5% active ingredient concentration is not intended to produce a pharmacological effect but is necessary to match taste, odor, and appearance for successful blinding. We acknowledge that this active control is not an inert placebo. Therefore, the design compares each PABG dose (low and high) against a low-dose active control. Any treatment effect may be underestimated (biased toward the null). This limitation is further discussed in Section 6.

### Randomization and blinding

2.10

A stratified block randomization sequence will be constructed using SAS software (version 9.4 or later; SAS Institute Inc., Cary, USA) by a team of randomization statisticians. The stratification is based on two factors: age categories (≥4 to ≤6 years, >6 to ≤10 years, >10 to ≤16 years) and baseline disease severity (YGTSS total score ≥25 to ≤50, >50).

All eligible participants will be randomly allocated to the high-dose PABG group, low-dose PABG group, or active control group at a 2:2:1 ratio via the Interactive Web Response System (IWRS). Authorized investigators will access the system to retrieve the participants’ treatment assignments for randomization. The outcomes of the randomization process will be strictly kept confidential.

Neither the participants nor the research team will be informed of the treatment assignments until the conclusion of the study. Emergency unblinding will be carried out through the IWRS in scenarios such as severe deterioration of participants’ conditions requiring emergency rescue or as mandated by regulatory authorities. The rationale, date, and time of unblinding will be documented in the electronic Case Report Form (eCRF), and the relevant participants will be classified as dropouts.

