### Discontinuation of study intervention

2.13

Participants can voluntarily withdraw from the study at any time and for any reason. All reasons and the time of discontinuation will be documented in the eCRFs and included in the subsequent analysis. Participants will be discontinued from the trial if any of the following events take place: (1) Adverse events of Grade 3 or higher that are considered by the investigator to be related to the study intervention; (2) Serious adverse events that are considered by the investigator to be related to the study intervention; (3) Death; (4) Withdrawal of informed consent by the participant; (5) Termination of the study by the sponsor.

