## Statistical analysis

4

All statistical analyses will be conducted according to a prespecified statistical analysis plan (SAP) by statisticians independent of the research team, who will remain blinded to treatment allocation. A two-sided *P* value <0.05 will be considered statistically significant, and 95% confidence intervals (CIs) will be used to estimate effect sizes. All analyses will be performed using SAS version 9.4 (SAS Institute Inc., Cary, NC, USA).

Continuous variables will be summarized according to their distribution using the number of observations, mean, standard deviation, median, 25th percentile (P25), 75th percentile (P75), and range. Categorical variables will be presented as frequencies and percentages. Demographic characteristics and baseline variables will be summarized descriptively.

For participants who withdraw, drop out, or discontinue treatment, the reasons for discontinuation and the time of the last dose will be recorded. Completed assessment data will be included in the statistical analyses, whereas incomplete data will be treated as missing. Missing data will be handled using multiple imputation methods.

Predefined subgroup analyses for the primary efficacy endpoint will be conducted by gender, age, TD severity and clinical subtype. Sensitivity analyses will include the impacts of prohibited concomitant medications and poor study drug adherence.

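### Emergency unblinding and stopping for related toxicity are merged with leaving the trial, so Week 8 YGTSS-TTS can be missing by rule for reasons linked to deterioration or harm

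*Protocol article*

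**What the plan says.** Four parts of the protocol article bear on this.

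- **Section 2.10 (Randomization and blinding).** "Emergency unblinding will be carried out through the IWRS in scenarios such as severe deterioration of participants" whose condition calls for emergency rescue, or when a regulator requires it. The reason and time are recorded, "and the relevant participants will be classified as dropouts".
- **Section 2.13 (Discontinuation of study intervention).** Under that heading the rule reads: "Participants will be discontinued from the trial if any of the following events take place". Five events follow. The first two are "Adverse events of Grade 3 or higher that are considered by the investigator to be related to the study intervention" and "Serious adverse events that are considered by the investigator to be related to the study intervention". The others are death, withdrawal of consent and termination by the sponsor. Unblinding is not on the list. The section also states: "All reasons and the time of discontinuation will be documented in the eCRFs and included in the subsequent analysis".
- **Section 4 (Statistical analysis).** For children who withdraw, drop out or discontinue, assessments already completed enter the analysis and the rest count as missing. "Missing data will be handled using multiple imputation methods". The sensitivity analyses named there concern prohibited medication and poor adherence.
- **Section 3.1 (Primary efficacy endpoints).** Both primary endpoints, the change in YGTSS-TTS and the proportion with at least a 30% reduction, are read at Week 8.

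**The concern.** Breaking the code for one child is not loss to follow-up, and neither is stopping the granules after a related adverse event. In both cases the child can usually still attend Week 8 and be scored. The article's rules nevertheless place these children with dropouts (Section 2.10) or with deaths and consent withdrawals (Section 2.13).

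The reasons for the loss are not random. Unblinding can follow severe deterioration, and the first two stopping criteria are harms attributed to study drug. A Week 8 value that goes missing for such a reason may differ systematically from the values that were observed. Multiple imputation in its usual form assumes that, given what is in the model, it does not. Section 5.1 relies on randomization to make natural improvement equal across groups, and losses after randomization that depend on outcome or harm weaken that argument. These gaps come from the plan's own classification and could be avoided.

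**Working it through.** **1. Side-by-side reading.** Section 2.10 makes unblinding an exit, while Section 2.13's list of exits omits it. Section 2.13's heading speaks of the intervention, while its rule speaks of the trial. Section 2.14 allows rescue treatment for inadequate control and names no exit. So a child with ordinary poor control can stay and be scored, while a child whose severe deterioration leads to unblinding becomes a dropout. The three rules need reconciling whatever the numbers are.

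**2. Inputs (Section 2.7).** Assumed mean reductions are 12.4 (low dose), 12.9 (high dose) and 8.2 (control), with SDs 6.8, 6.6 and 7.0. Arm sizes are 60, 60 and 30. Baseline YGTSS-TTS is 22.8. The plan's contrasts reproduce: 12.4 − 8.2 = 4.2 and 12.9 − 8.2 = 4.7. The article gives no count of children expected to be unblinded or stopped for toxicity, and no figure for their Week 8 scores. Those are assumptions below.

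**3. Shift per lost child.** Suppose the missing value is filled at the arm mean. The arm mean is then overstated by (arm mean − true reduction) / n.

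| Arm | True reduction is half the arm mean | True reduction is 0 | True worsening of 5 |
|---|---|---|---|
| Low dose, n = 60 | 6.2/60 = 0.10 | 12.4/60 = 0.21 | 17.4/60 = 0.29 |
| High dose, n = 60 | 6.45/60 = 0.11 | 12.9/60 = 0.22 | 17.9/60 = 0.30 |
| Control, n = 30 | 4.1/30 = 0.14 | 8.2/30 = 0.27 | 13.2/30 = 0.44 |

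Relative to the low-dose contrast, 0.29/4.2 is about 7% and 0.44/4.2 about 10%, per child.

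**4. Sign.** A shift in a PABG arm adds to the contrast, and a shift in control subtracts from it. If both arms lose children at the same rate, say 2 of 60 low-dose and 1 of 30 control, each with a true worsening of 5, the net effect is 2 × 0.29 − 0.44 = +0.14.

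**5. What earlier visits recover.** A large-sample simulation used the planning means and SDs and lost every child whose true Week 8 change was a worsening. That is about 12% of control and 2.5% to 3.4% of the dose arms. The high-dose contrast fell from 4.7 to 3.5 with arm-mean imputation, and to 4.0 when one earlier visit entered the imputation (within-child correlation 0.7, assumed). The low-dose contrast fell from 4.2 to 3.1 and 3.6 respectively. In this scenario the bias is toward the null, and earlier visits remove only part of it.

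**6. Responder endpoint.** A 30% reduction from 22.8 is 6.84 points. Taking reductions as normal with the planning values (an assumption), response rates are Φ((12.9 − 6.84)/6.6) = 82% for high dose and Φ((8.2 − 6.84)/7.0) = 58% for control. A true non-responder imputed at the arm's rate adds 0.82/60 = 1.4 percentage points in the high-dose arm or 0.58/30 = 1.9 in control.

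**The case against.** The strongest reply is that the article removes nobody. Section 4 keeps completed assessments, Section 2.13 carries reasons and timing into the analysis, and no section excludes dropouts from an analysis set. Analysis sets and the imputation model normally belong to the SAP, which is not shown. The wording in Section 2.13 about the trial may be loose condensation of a fuller protocol, and it does not expressly forbid later assessments. Most children with poor tic control fall under Section 2.14, not Section 2.10. All of this is fair and limits the point, but it does not dispose of it. Keeping earlier assessments does not supply the Week 8 value, and the classification as dropouts is a stated rule, not something left to the SAP.

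Several stronger readings are tempting, but the documents do not support them:

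- **That these children are deleted and the intention-to-treat comparison is broken.** The text says only that uncompleted assessments are missing.
- **That they are imputed from children who did well.** The model is not given and could use the child's own Week 2, 4 and 6 scores.
- **That the worst outcomes are the ones lost.** Related toxicity is not a poor tic score, and unblinding required by a regulator need not reflect outcome.
- **That safety follow-up is lost.** Section 2.11 records treatments for drug-related events for 4 weeks after the last dose, including in early stoppers, and Section 3.3 records the outcome of adverse events. What is unclear is whether scheduled safety visits continue.
- **That the distortion is 14% to 31% of the effect.** Two low-dose losses (2 × 0.29 = 0.58) and three control losses (3 × 0.44 = 1.32) can be made to look like one range of this kind against 4.2. They have opposite signs, and the counts come from nowhere in the article.

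**Conclusion.** The point holds as a defect in stated rules. Sections 2.10 and 2.13 merge loss of blinding and stopping study drug with leaving the trial, so Week 8 YGTSS-TTS can be missing by rule for reasons tied to deterioration or harm. Section 4 then imputes it.

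The direction of bias is not determined. It inflates the contrast if losses fall mainly in the PABG arms, which is plausible for toxicity, and dilutes it if they fall mainly in control, which is plausible for deterioration. The size cannot be fixed from the article. The figures of about 0.29 points per low-dose child and 0.44 per control child rest on two assumptions, imputation at the arm mean and a true 5-point worsening. Both get smaller if the true value is less extreme or if earlier visits enter the model. With few such children the effect is modest, although each loss weighs most in the 30-child control arm. The correction is worth making because the missing data are avoidable at little cost.

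**What to change.** Reconcile Sections 2.10, 2.13 and 4, leaving the unblinding triggers and stopping criteria as they are.

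1. In Section 2.10, replace the classification as dropouts with a statement that emergency-unblinded children stay in the analysis as randomized, with the unblinding recorded as an event.
2. In Section 2.13, separate stopping study medication from leaving the trial. Children who meet the two adverse-event criteria keep the already scheduled Week 8 YGTSS and safety visits unless consent is withdrawn.
3. In Section 4, make clear that a value counts as missing only when the assessment was not done, and add a sensitivity analysis that flags Week 8 ratings made after the code was known.

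Two further choices are open to the sponsor, and the point does not depend on them: a rater unaware of the code, which may need extra staff, and counting unblinding for deterioration as non-response, which is a choice of estimand.

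The cost is a few sentences and some already scheduled visits by children off study drug. The drawback is that some of those ratings will be made with the allocation known, which is why they need flagging. Recruitment is expected to run to 31 December 2026 (Section 5.2), so the change can be made before enrolment is due to close.

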### Concomitant care

2.11

Participants must not use other medications for the treatment of TD to avoid interference with PABG efficacy. Concomitant medications and treatments will be documented at each visit from ICF signature through the treatment period, with details recorded in the eCRF. Concomitant treatments for study drug-related adverse events within 4 weeks after the last dose will also be recorded for all subjects who complete treatment or discontinue early.

### Monitoring compliance

2.12

Participants and their legal guardians will be instructed to record the number of sachets consumed each week. During the treatment period, unused study medication and packaging will be collected at each follow-up visit. The quantity of consumed and returned study medication will be documented in the eCRF to assess medication adherence. A compliance rate of ≥80% will be defined as high adherence.

### Discontinuation of study intervention

2.13

Participants can voluntarily withdraw from the study at any time and for any reason. All reasons and the time of discontinuation will be documented in the eCRFs and included in the subsequent analysis. Participants will be discontinued from the trial if any of the following events take place: (1) Adverse events of Grade 3 or higher that are considered by the investigator to be related to the study intervention; (2) Serious adverse events that are considered by the investigator to be related to the study intervention; (3) Death; (4) Withdrawal of informed consent by the participant; (5) Termination of the study by the sponsor.

### Rescue treatment

2.14

If a participant shows inadequate disease control (no improvement in tic symptoms after at least 4 weeks of study medication) and symptoms remain unrelieved after elimination of potential triggers, rescue treatment with tiapride 50 mg daily may be used. The discontinuation time will be determined by the investigator based on subsequent YGTSS scores.

The investigators must document all details of rescue treatment in the eCRF, including the medication name, duration, dosage, and the participant’s response.

## Assessments and endpoints

3

This study will employ the internationally recognized and widely used Yale Global Tic Severity Scale (YGTSS) (42), which concurrently assesses tic symptoms and social functioning in children with TD. Its core measurement dimensions, abbreviations, and scoring criteria are described as follows: (1) YGTSS–Total Tic Score (YGTSS-TTS): the sum of motor tic scores (0–25 points) and vocal tic scores (0–25 points), with a total score ranging from 0 to 50 points. It quantifies the severity of both motor and vocal tics and reflects the overall tic symptom burden. (2) YGTSS-Impairment Score (YGTSS-IS): ranging from 0 to 50 points, it quantifies the overall impairment of tic symptoms on patients’ daily functioning, covering core domains including social interaction, academic performance, family life, and self-esteem. The YGTSS Total Score is the sum of YGTSS-TTS and YGTSS-IS, with a scoring range of 0–100 points. Severity grading is defined as follows: a YGTSS Total Score <25 points indicate mild severity, 25–50 points indicate moderate severity, and >50 points indicate severe disease (43).

This study will additionally adopt the TCM-SRS published by the Pediatrics Branch of the Chinese Association of Chinese Medicine (CACM) in 2013, with detailed scoring criteria presented in Figure 3. Concurrently, the C&A-GTS-QoL will be incorporated for efficacy assessment.

**Figure 3 fig3:**
[figure not shown]
TCM-SRS for tic disorder severity grading.

Schedule of study assessments and procedures across all time points is summarized in Figure 4.

**Figure 4 fig4:**
[figure not shown]
Schedule of trial.

### Primary efficacy endpoints

3.1

The change in YGTSS-TTS from baseline and the proportion of participants achieving a ≥ 30% reduction in YGTSS-TTS, both assessed at Week 8.

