### Sample size

2.7

To date, no active-controlled trial has evaluated PABG for the treatment of tic disorders with SDPWS. The primary endpoint of this study is the change from baseline in the YGTSS–Tic Severity Score (YGTSS-TTS) at Week 8. Preliminary data from our pilot study indicated a mean baseline YGTSS-TTS score of 22.8. The minimal clinically important difference (MCID) for the YGTSS-TTS is defined as a ≥ 25% reduction from baseline (39), corresponding to 5.7 points. Based on effect sizes reported in clinical trials of comparable Chinese patent medicines for tic disorders (40), and considering the dose-gradient design of the present study, we assume a mean reduction of 8.2 ± 7.0 points in the active control group, 12.4 ± 6.8 points in the low-dose group, and 12.9 ± 6.6 points in the high-dose group.

With a two-sided significance level of *α* = 0.025 (Bonferroni correction for two comparisons: high-dose vs. active control and low-dose vs. active control) and *β* = 0.20 (80% power), and an allocation ratio of 2:2:1, the sample size was calculated using PASS version 20.0 (NCSS, LLC, Kaysville, UT, USA). Allowing for a 15% dropout rate, the adjusted and rounded total sample size was determined to be 150 participants, with 60 in the high-dose group, 60 in the low-dose group, and 30 in the active control group. The primary comparisons are each active dose versus the active control; the sample size was not powered to detect a statistically significant difference between the two active doses. The close projected outcomes (0.5-point difference) reflect a conservative assumption, and the dose–response assessment is exploratory.

The assumed effect size between each active dose and the active control (approximately 4.2 to 4.7 points) is consistent with the effect observed in a previous trial of a similar Chinese patent medicine (40), where the active product showed a 4.8 point greater reduction in YGTSS-TTS compared with placebo at week 8. Although this effect is slightly below the MCID of 5.7 points, as an exploratory dose-finding trial, any statistically significant signal, even if below the MCID, would support further investigation in a larger confirmatory trial. The MCID will be used for clinical interpretation of the final results.

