### Primary outcomes

4.1

The change from baseline in YGTSS-TTS at Week 8 will be compared between groups using analysis of covariance (ANCOVA), with treatment group, baseline value, and randomization stratification factors included as covariates. Least-squares means, standard errors, and 95% CIs for the change scores, as well as least-squares mean differences with 95% CIs between groups, will be estimated.The proportion of participants achieving a ≥ 30% reduction in YGTSS-TTS from baseline at Week 8 will be calculated with 95% CIs using the Wilson score method. Between-group differences in response rates will be estimated with 95% CIs using the stratified Newcombe method, and group comparisons will be performed using the stratified Cochran–Mantel–Haenszel (CMH) test.

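### Section 2.7 sizes one primary endpoint; the abstract and sections 3.1 and 4.1 add a second, a ≥30% responder rate on the same score, with about 20 points less power

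*Protocol article*

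**What the plan says.** Section 2.7 (Sample size) speaks of a single endpoint: "The primary endpoint of this study is the change from baseline in the YGTSS–Tic Severity Score (YGTSS-TTS) at Week 8". The arm means and SDs, the 80% power, the two-sided 0.025 per comparison and the total of 150 (60 high, 60 low, 30 control) all belong to that change score.

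Section 3.1 lists two primary endpoints at the same visit: the change in YGTSS-TTS and "the proportion of participants achieving a ≥ 30% reduction in YGTSS-TTS, both assessed at Week 8". The abstract does the same. Section 4.1 analyses the change by ANCOVA. For the responder rate it plans Wilson intervals and a stratified Newcombe difference, and "group comparisons will be performed using the stratified Cochran–Mantel–Haenszel (CMH) test".

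Section 3.2 already holds the ≥30% responder rates at the other visits and the ≥50% rate at all visits, Week 8 included, as secondary endpoints.

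**The concern.** The article disagrees with itself on how many primary endpoints there are. The one that section 2.7 leaves out is a cut of the same 0–50 score at the same visit, so it uses less of the information in the data. It nevertheless gets its own between-group test at primary rank.

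If the drug works as section 2.7 assumes, the two primary results can easily disagree: a clear difference on the change score beside a non-significant responder rate. The reader would have no stated basis for knowing that this was likely from the design.

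**Working it through.** **Inputs (section 2.7).** "a mean baseline YGTSS-TTS score of 22.8"; "we assume a mean reduction of 8.2 ± 7.0 points in the active control group"; "12.4 ± 6.8 points in the low-dose group"; high dose 12.9 (SD 6.6); two-sided alpha 0.025 per comparison; 60:60:30; 15% dropout. Section 4 also gives a general threshold of P<0.05, so both levels are shown.

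**Step 1. The plan's own figure.** For the change score with two treated children per control, evaluable controls needed = (z₀.₉₈₇₅ + z₀.₈₀)² × (SD_c² + SD_t²/2) / Δ², where (2.241 + 0.842)² = 9.505.
- Low: 9.505 × (49 + 23.12) / 4.2² = 38.9, so 39 controls. The total is 5 × 39 = 195, or 230 after dropout.
- High: 9.505 × (49 + 21.78) / 4.7² = 30.5, so 31 controls. The total is 155, or 183 after dropout.

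The stated 150 does not reproduce at two-sided 0.025. It is close only for the high dose with 0.025 used one-sided: 26 controls and 130 evaluable, giving 150 as 130 × 1.15 or 153 as 130 / 0.85. That shortfall is a separate matter. Here it means that the change score must be compared at its actual power, not at 80%.

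**Step 2. Implied responder rates.** The cut is 0.30 × 22.8 = 6.84 points. With normal change scores, the rate is Φ((mean − 6.84)/SD).
- Control: Φ(1.36/7.0) = Φ(0.194) = 0.577
- Low: Φ(5.56/6.8) = Φ(0.818) = 0.793
- High: Φ(6.06/6.6) = Φ(0.918) = 0.821

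**Step 3. Power.** Responder endpoint: exact binomial enumeration of the unstratified Mantel–Haenszel chi-square. Change score: two-sample noncentral t with pooled SD. After dropout, 51 versus 25 are evaluable.

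| Setting | Responder, low / high | Change score, low / high |
|---|---|---|
| 60 vs 30, alpha 0.025 | 47% / 59% | 68% / 80% |
| 51 vs 25, alpha 0.025 | 39% / 51% | 59% / 72% |
| 60 vs 30, alpha 0.05 | 57% / 70% | 77% / 87% |
| 51 vs 25, alpha 0.05 | 51% / 63% | 70% / 81% |

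Hand check, low dose, 60 vs 30, alpha 0.025, normal approximation: the pooled rate is 0.721, the null SE 0.1003 and the alternative SE 0.1043. Power = Φ((0.216 − 2.241 × 0.1003)/0.1043) = Φ(−0.08) = 47%. Using 25.5 evaluable controls instead of 25, the same approximation gives 40% and 52% for responders and 60% and 72% for the change score, so the rounding does not matter.

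**Step 4. Does the position of the cut matter?** Responder power at 60 vs 30 and alpha 0.025:

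| Cut | Low | High |
|---|---|---|
| 25% | 44% | 57% |
| 30% | 47% | 59% |
| 36% | 49% | 61% |
| 40% | 48% | 61% |
| 50% | 44% | 55% |

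The 30% cut is within about two points of the best available.

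**Step 5. Sensitivity.** Section 2.7 gives no baseline SD. Simulations assumed SD 4 to 8 and a baseline–change correlation of 0 to 0.5, after dropout, at alpha 0.025. The control rate stays at 57–59%. Responder power runs from 39% to 52% (low) and 48% to 66% (high). Against ANCOVA in the same simulations, the loss is 18 to 26 points.

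**Step 6. Size needed.** At alpha 0.025, 80% power on the responder test takes about 63 evaluable controls (low) or 47 to 48 (high). That is 63 × 5 / 0.85 = 371 randomised, or 277 to 283.

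**The case against.** Several stronger readings are tempting, and the article does not support them.

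- **The threshold is at fault.** The assumed control mean (8.2 points, 36% of baseline) lies above the 30% cut, and a reader might infer that this causes the power loss. Step 4 shows that it does not: every cut from 25% to 50% gives 44–49% for the low dose.
- **The plan claims 80% power for both endpoints.** It does not. Section 2.7 ties that figure to the change score.
- **Both primaries must succeed, so the chance of a positive trial falls.** No section says so. Section 2.7 calls the trial exploratory and would take any significant signal as support for further work.
- **A truly effective low dose is more likely than not to miss on responders.** That holds at 0.025 with an unvarying baseline, but at 0.05 the odds are even or better. A baseline–change correlation of 0.5 also brings them to about even at 0.025. Section 4 plans multiple imputation, so the complete-case counts are only an approximation.
- **The responder rate adds nothing.** That goes too far. The assumed differences of 4.2 to 4.7 points are below the article's MCID of 5.7, so a per-child rate helps interpretation.

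The defence can also say that the change score stays primary with its own power intact, and that the full protocol or the guideline cited in the Introduction may justify the 30% cut. Both points are fair. Neither reconciles one primary endpoint in section 2.7 with two in section 3.1, and neither supplies power for the second.

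**Conclusion.** The point stands as an inconsistency with a measurable consequence. Section 2.7 names and sizes one primary endpoint, while the abstract and sections 3.1 and 4.1 carry a second, tested one that was never sized. On the article's own assumptions its power is roughly 20 points below that of the change score at either alpha, with or without dropout. It is well short of 80% for both doses.

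This rests on roughly normal change scores, the pilot baseline of 22.8, an unstratified approximation to the planned CMH test and complete cases. Varying the baseline changes the absolute figures, but the gap to ANCOVA remains.

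**What to change.** In the abstract and sections 3.1 and 4.1, make the Week 8 change in YGTSS-TTS the sole primary endpoint, as section 2.7 already has it. Move the Week 8 ≥30% responder rate to section 3.2, beside the ≥50% rate. Report it by arm with its stratified difference and confidence interval, as a clinical reading of the continuous result.

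If it must remain primary, state in section 2.7 the implied rates (about 58%, 79% and 82%) and the power that follows from them, and say that the 80% figure applies to the change score only. Do not move the threshold in the hope of regaining power.

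The cost is wording in the protocol and analysis plan, and an update of the registry entry where it lists the responder rate as primary, made before unblinding. No patients, visits or data are added. The downside is that the responder rate no longer carries a primary claim.
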